# Effects of two types of exercise training on psychological well-being, sleep, quality of life and physical fitness in patients with high-grade glioma (WHO III and IV): study protocol for a randomized controlled trial

**DOI:** 10.1186/s40880-019-0390-8

**Published:** 2019-08-09

**Keywords:** Brain, Tumor, Glioma, Exercise, Training, Sleep, Control condition, Quality of life, Anxiety, Perceived stress

## Abstract

**Background:**

There is existing evidence on whether and to what degree regular exercise training improves the quality of life (QoL) among cancer survivors. However, in regards to patients with high-grade glioma (HGG; WHO grade III and IV), no conclusive study has been performed so far. The present trial aims to fill this gap by examining whether psychological well-being, sleep, QoL and physical fitness might be improved with two different types of exercise, as compared to an active control condition. Active control condition represent individuals participating at regular meetings to talk about their current life situation, though, the meetings were not intended as that of the psychotherapy group. Regular meetings are of the same frequency, duration, and intensity as the exercise interventions.

**Methods:**

A total of 45 patients with HGG after undergoing neurosurgery and adjuvant radiotherapy, chemotherapy, or chemoradiotherapy will be consecutively and randomly assigned to (a) an endurance training, (b) a resistance training or (c) to an active control condition. The intervention will last for 6 consecutive weeks, consisting of 2 weekly sessions (30–45 min per session). Measurements would take place at three time points, namely at the beginning of the study (baseline), 3 weeks after the beginning of the study, and 6 weeks after the beginning of the study. The last measurement also represents the end of the study. Aerobic exercise performance will be assessed objectively with a 6-min walking test, and a handgrip test will be used to assess the upper body strength. Further, participants will complete a battery of questionnaires covering sociodemographic information, QoL, sleep quality and sleep patterns, coping with stress, state- and trait-anxiety, depression, and fatigue. In parallel, experts will use the Hamilton Depression Rating Scale to determine and rate participants’ symptoms of depression.

**Significance:**

The present study will be the first to investigate and compare the impact of two different exercise modalities, namely endurance and resistance training, on physical fitness and dimensions of well-being, and sleep among patients with HGG who underwent neurosurgery followed by adjuvant radiotherapy, chemotherapy, or chemoradiotherapy. Importantly, unlike the majority of previous studies, the control condition consists of an active set-up to detect possible factual beneficial effects of exercise training, irrespective of social interactions.

*Trial registration*
https://register.clinicaltrials.gov; identifier: NCT03775369

## Background

There is increasing evidence that cancer survivors benefit from adjuvant exercise training to improve their subjective wellbeing, and improvements have been observed in regards to quality of life (QoL), coping with stress, and self-control. Here, self-control refers to the individual’s ability to control her/his thoughts, emotions, and behavior. Exercise training also has the potential to counteract series of side-effects of chemotherapy or hormone therapy such as fatigue, weight gain, muscle loss, hot flushes, nausea, or increased susceptibility to infections [1, 2]. Further, Segal et al. [3] underlined in their systematic review that exercise training is a safe intervention, which provides benefits with regard to quality of life, and muscular and aerobic performance both during and after cancer-specific treatment. However, a deeper inspection of the type of cancer reported in the systematic review of Segal et al. [3] revealed that randomized clinical trials were performed for breast cancer, colorectal cancer, prostate cancer, or just mentioned ‘cancer’ without further specifications on the location, while no randomized clinical trial has yet tested the influence of exercise interventions in patients with glioma, and more specifically with high grade glioma (HGG; WHO grade III and IV). Thus, the present randomized clinical trial was designed to address this research gap, and to create an empirical evidence base on whether exercise training can be seen as a treatment option among patients with HGG during the post-surgery state in order to improve their wellbeing, sleep and QoL.

As mentioned by Ostrom et al. [4, 5] gliomas represent 31% of all malignant brain tumors and 81% of central nervous system (CNS) tumors diagnosed in the United States. Although gliomas are rare, they can still lead to significant mortality and morbidity. Further, not all types of gliomas develop in an aggressive way, and the heterogeneity of these gliomas in terms of histopathological types and grades, clinical outcomes, and genomics makes treatment and risk management even more difficult [6].

As regards to the identification of possible risk factors, Ostrom et al. [5, 6] summarized in their systematic review that ionizing radiation and heritable genetic variants appeared to increase the risk for gliomas, whereas allergies and atopic diseases appeared to be protective. However, there is inconclusive evidence of non-ionizing radiation via cell phone use and risk of gliomas.

The usual treatment algorithm for high-grade glioma consists of neurosurgical resection of tumor tissue and postoperative combined radiochemotherapy. Depending on the genetic sub-classification of the glioma and patient-specific factors such as age and clinical condition, postoperative treatment is sometimes given in the form of only radiation therapy or chemotherapy. In the present study, however, we will investigate whether and to what degree structured exercise training may have a (beneficial) effect on the psychological wellbeing, sleep, QoL, and physical fitness during the phase of postoperative adjuvant treatment.

The underlying rationales and research findings are as follows: On a physiological level, some scholars emphasize that regular exercise training has the potential to increase the levels of serotonin, brain-derived neurotrophic factor (BDNF) and endothelial growth factor (VEGF) [7], and to increase mitochondrial activity [8]. On the psychological level, other scholars argue that exercise training has the potential to improve the patients’ mood [9, 10] and self-esteem [11], to decrease symptoms of depression [12–17], anxiety, chronic pain [18], and above all rumination [19]. Further, in a previous study on the post-treatment of patients with post-aneurysmal subarachnoid hemorrhage, we have shown that compared to a control group, a 12-week regular endurance and resistance training ameliorated the symptoms of depression, insomnia and cognitive capacities [20–22]. Next, as regards to cancer survivors, most studies focused on breast cancer survivors during or after treatment [1]. Segal et al. [23] further emphasized that physical activity and exercise interventions were safe, provided benefit in quality of life, and might have the potential to enhance social exchange. In this respect, Brand et al. [19] showed that a single session of exercise could increase interest in social contact and interactions, at least among their investigated 129 inpatients (mean age: 38.16 years; median: 36.00 years; age range: 19–63 years) with a broad variety of psychiatric disorders. However, in regards to patients with HGG, to the best of our knowledge, there has been no study to investigate the impact of exercising on the patients’ well-being and QoL, despite it is well-acknowledged that individuals with HGG who underwent radiotherapy, chemotherapy, or both radio- and chemotherapy suffer from a dramatically decreased in QoL. Accordingly, the primary aim of the present study is to examine and compare the effects of two different types of exercise training (endurance vs. resistance) on psychological wellbeing (i.e., depression, stress, anxiety), sleep, QoL and physical fitness in patients with HGG who had neurosurgery followed by radiotherapy, chemotherapy, or both, compared to an active control condition.

## Methods

### Trial design

The present study is an interventional, and randomized clinical trial. Each patient will participate for 6 weeks, with pre-specified assessment time points (Table 1): Measurements would take place at three time points, namely, baseline, which is the start of the study after the randomization. The second time point is 3 weeks after the baseline/beginning of the study. The third and last time point is 6 weeks after the baseline/beginning of the study, which also represents the end of the study. After written informed consent is obtained, eligible participants from the Basel University Hospital (Department of Neurosurgery; USB, Basel, Switzerland) are to be randomly and consecutively assigned to one of the following study grouped-conditions (Fig. 1): (a) endurance training, (b) resistance training, and (c) active control.

**Table 1 Tab1:** Flow chart of the study: time points and the assessed dimensions at the time points

Outcome dimensions and time points	Time points				
	− 4 to − 1 weeks^a^	− 1 week	Week 0	Week 3	Week 6
Diagnosis and surgery	X				
Chemotherapy and/or radiotherapy at the same time			X X		
Patient’s eligibility is checked		X			
Signed written informed consent					
Randomization		X			
Assessment					
Cardiovascular performance (6MWT) and grip strength			X	X	X
Psychological functioning			X	X	X
Start study interventions			X		
Interventions			X X		
Study end					X

*6MWT* 6-min walking test, *X* this dimension is assessed; blue arrow, the time point from one period to the next

^a^− 4 to − 1 weeks, 4 weeks to 1 week of pre-treatment period

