### Participant timeline

As shown in Table 1, patients from the Department of Neurosurgery of the Basel University Hospital (Basel, Switzerland) have the following timeline: After neurosurgical treatment of the HGG, the patients would undergo either chemotherapy, or radiotherapy, or both. In parallel, they would be informed about the study content and the study aims. Once the written informed consent is signed, and the baseline assessment (cardiovascular performance and grip strengths; psychological assessments) (Table 1) is completed, the patients will be randomly assigned to one of the three study conditions. For the next 6 consecutive weeks, she/he would follow the schedule with two sessions per week. After the 3rd and 6th weeks, from the start of the study, the patients would be reassessed; similar as to the baseline assessments.

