### Randomization

The randomizations are to be performed using an online software from the website Randomization.com (http://www.randomization.com). The online generator randomizes each subject to a single treatment using a method of randomly permuted blocks, with random block sizes for sex. Based on the generated list, a psychologist, not involved in the study, prepares 45 sealed envelopes, with no further identification, to be kept in an opaque and closed ballot box which are to be stirred before picking. Next, the psychologist would draw an envelope from the ballot and assign the study participants to one of the three study conditions picked. Once an envelope is drawn, it would be put aside. Experts rating the participants’ depression severity would be blinded to the participants’ study condition assigned.

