#### Psychological wellbeing

A set of self-report questionnaires will be used to assess the patients’ psychological wellbeing, including symptoms of depression, state- and trait-anxiety, and perceived stress. All questionnaires will be completed at baseline, 3 weeks into the study, and at the end of the study.

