#### Physical fitness

To assess physical fitness, all participants will perform the 6-min walking test (6MWT) and handgrip strength test at baseline and at the end of the study.

We will use the 6MWT as a measure of cardiorespiratory fitness [42]. The 6MWT is a standardized, self-paced, submaximal exercise test, and has been designed especially for patients suffering from chronic diseases. Evidence of the validity of the 6MWT has been previously shown in various disease types [43–45] including cancer patients [46, 47]. The walking distance will be used as the main outcome measure of the 6MWT. Oxygen saturation before and after the 6MWT will be also taken into consideration.

As a measure of upper body strength, we will perform the grip strength test. As described elsewhere [48], maximum isometric grip force of the dominant hand would be assessed using a mechanic hand dynamometer (Jamar Handgrip Dynamometer; retailer: Rehaforum MEDICAL GmbH; Elmshorn, Germany). Participants will have three attempts per hand. The validity of the grip strength test has been previously documented, and researchers have shown that grip strength is associated with psychological wellbeing across different populations [49].

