### Statistical analyses

Irrespective of which study conditions the patients are grouped to, at baseline, we will use Pearson’s correlations and univariate ANOVAs to examine the associations between the participants’ social and demographic background and their psychological wellbeing, sleep, QoL, and physical fitness. To examine whether and to what degree the three study conditions (endurance training, resistance training, active control) would impact the outcome variables over time, a series of ANOVAs for repeated measures with the following factors and dependent variables will be performed, namely, time (baseline; week-3 and week 6 since start of study); group (endurance training; resistance training; active control), and the time-by-group interaction; dependent variables: depressive symptoms, anxiety, stress, sleep complaints, QoL, cardiorespiratory fitness, and grip strength. Given the explorative character of the present study, we follow the previously reported recommendations [50, 51] and no correction of p-values for multiple testing would be performed. Data would be analyzed both per protocol and by intent-to-treat (ITT), with the last observation carried forward (LOCF). Patients will not be further followed up as regards the study questions, though, they would undergo routine checks every 6 months to monitor the development and recovery process of the HGG. The level of significance is set at alpha ≤ 0.05. All computations would be performed with the Statistical Package for the Social Sciences (SPSS)^®^ software (IBM Corporation, Armonk NY, USA) for Macintosh^®^.

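### Baseline falls after randomisation in the trial design section and Table 1 but before it in the participant timeline; the first order leaves the baseline measures open to knowledge of the arm.

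*Protocol article*

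**What the plan says.** The protocol article gives the order of baseline and randomisation in three places.

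- **Trial design, text:** the first time point is "baseline, which is the start of the study after the randomization".
- **Trial design, Table 1:** the Randomization row is marked at week -1. The first mark in the row "Cardiovascular performance (6MWT) and grip strength", and the first mark for psychological functioning, are at week 0, the column in which the interventions start.
- **Participant timeline:** "Once the written informed consent is signed, and the baseline assessment" (tests and questionnaires) "is completed, the patients will be randomly assigned to one of the three study conditions". This section cites Table 1 for its sequence, although Table 1 shows the opposite.

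Four further statements determine whether the order matters.

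- **Blinding** is stated for one group only: "Experts rating the participants’ depression severity would be blinded to the participants’ study condition assigned" (Randomization).
- **Psychological outcomes** are mainly patient-reported: "A set of self-report questionnaires will be used to assess the patients’ psychological wellbeing" (Psychological wellbeing).
- **The walking test** depends on effort: "The 6MWT is a standardized, self-paced, submaximal exercise test" (Physical fitness).
- **The analysis** is a repeated-measures ANOVA with factors "time (baseline; week-3 and week 6 since start of study); group (endurance training; resistance training; active control), and the time-by-group interaction" (Statistical analyses). It is run per protocol and by intention to treat, with the last observation carried forward.

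**The concern.** Site staff cannot follow both orders, and the choice between them is not neutral. The three conditions are a treadmill programme, a resistance programme and a discussion group, so a patient who has been told the allocation cannot be blind to it. If the first questionnaires, walking test and grip test come after that, the answers and the effort can already reflect disappointment or enthusiasm about the arm. The supposed pre-treatment value is then no longer free of the allocation.

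Baseline is one of the three levels of the time factor, so it helps define every time-by-group interaction. A disturbance of baseline that differs between arms and later fades looks like a difference in change over time.

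The second stake is the intention-to-treat set. Under the Table 1 order, a patient can be randomised at week -1 and leave before any measurement. Carrying the last observation forward cannot help, because there is none. Under the timeline order every randomised patient has a baseline value.

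**Working it through.** **Step 1. Is the contradiction real?** Broken table extraction does not explain it. The Trial design prose puts baseline after randomisation without help from the table, and the Participant timeline prose puts it before.

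**Step 2. Reproduce the plan's own figure, to fix the model.** Inputs from Sample size calculation: f = 0.25, alpha = 0.05, power 0.80, k = 3 groups, m = 3 measurements, N = 36, raised to 45 (15 per group). Assumed because not given: correlation rho = 0.5 and sphericity (epsilon = 1).

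- lambda = f² × N × m / (1 − rho) = 0.0625 × 36 × 3 / 0.5 = 13.5
- df1 = (k − 1)(m − 1) = 4; df2 = (N − k)(m − 1) = 33 × 2 = 66
- Power = 0.823. The smallest N reaching 0.80 is 35, or 36 with equal groups.

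The stated 36 is reproduced at rho = 0.5. The order of baseline and randomisation does not enter this calculation, so the fix changes no sample-size figure.

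**Step 3. Effect of a shifted baseline on the planned test.** The article gives no size for such a shift, so the values of b below are assumptions. Suppose there is no true effect, but baseline in both exercise arms differs from control by b SD because the arm is known, and the shift is gone by weeks 3 and 6.

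- Group deviations at baseline: b/3, b/3, −2b/3; sum of squares 2b²/3.
- Time pattern of a baseline-only shift: 2/3, −1/3, −1/3; sum of squares 2/3.
- Interaction sum of squares = (2b²/3) × (2/3) = 4b²/9.
- lambda = 15 × (4b²/9) / (1 − rho), with df1 = 4 and df2 = 42 × 2 = 84.
- For b = 0.2 and rho = 0.5: lambda = 15 × 0.16 / 9 / 0.5 = 0.533.

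Rejection rate of the nominal 5% interaction test at N = 45:

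| Assumed b | rho = 0.3 | rho = 0.5 | rho = 0.7 |
|---|---|---|---|
| 0.2 SD | 0.069 | 0.076 | 0.096 |
| 0.3 SD | 0.094 | 0.114 | 0.164 |
| 0.5 SD | 0.189 | 0.256 | 0.415 |

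**Step 4. What if the shift persists?** If a fraction p of the shift is still present at weeks 3 and 6, only b(1 − p) enters the interaction; the rest goes to the group main effect. With b = 0.2 and p = 0.5 the effective shift is 0.1 SD and the rejection rate at rho = 0.5 is 0.056. With p = 1 it is 0.05.

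**Step 5. Direction.** Take one exercise arm against control on change from baseline, with rho = 0.5.

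- Variance of a change = 2(1 − 0.5) = 1 SD², so SE = sqrt(2/15) = 0.365 SD.
- A fully transient 0.2 SD shift is 0.2 / 0.365 = 0.548 SE.
- P(Z > 1.96 − 0.548) = 0.079; P(Z < −1.96 − 0.548) = 0.006.

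If exercisers start better, or controls start worse, because they know their arm, exercise shows less improvement. The 0.079 is then false rejection against exercise, and false rejection in its favour falls from 0.025 to 0.006. The sum, 0.085, belongs to this pairwise contrast; the planned three-group interaction gives 0.076 for the same shift.

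**The case against.** The best defence is that the harm is conditional. If the timeline order is what is done, nothing is biased. If the Table 1 order is done, bias still requires that patients or testers know the arm before week 0. The article does not say when allocation is disclosed, and a psychologist outside the study draws the envelope. A shift that lasts throughout cancels from the interaction. The trial also calls itself explorative. All of this stands, and it limits what can be said about size. It does not remove the contradiction, and nothing in the article withholds allocation until baseline has been recorded.

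Three stronger readings are tempting and are not supported:

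- **That every outcome is biased one for one.** The expert depression raters are blinded, although the patients they rate are not, and the full shift enters only if it has vanished by weeks 3 and 6.
- **That the plan is more likely to claim a false benefit of exercise.** Under the natural mechanism, Step 5 shows the reverse.
- **That the repair is wording only.** Table 1 has randomisation a week before assessment and start of sessions, so changing the order moves one of them.

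The loss of patients between week -1 and week 0 cannot be quantified from the article.

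**Conclusion.** The article contradicts itself on whether baseline precedes or follows randomisation, and this should be fixed. Confidence in the contradiction is high.

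Confidence in the size of the bias is moderate. It rests on four assumptions: that the Table 1 order is used, that the arm is known before the week-0 tests, that the shift is of the assumed size, and that it fades by weeks 3 and 6. Under all four, with 45 patients and rho = 0.5, the 5% interaction test rejects at about 7.6%, 11% or 26% for shifts of 0.2, 0.3 or 0.5 SD. Persistence reduces these figures. If disappointed controls score worse or enthusiastic exercisers score better at baseline, the error runs mainly against exercise.

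The gap in the intention-to-treat analysis does not depend on disclosure or on any assumed shift. It follows from the Table 1 order as soon as one randomised patient leaves before week 0.

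**What to change.** Use the Participant timeline order everywhere: consent, then complete and record all baseline tests and questionnaires, then draw the envelope. Specifically:

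1. Correct the Trial design sentence so that baseline precedes randomisation.
2. Move the Randomization mark in Table 1 to after the baseline assessment.
3. State that no envelope is drawn until the baseline data are recorded.

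The cost is small but not nil. Either baseline testing moves to week -1, which changes the point from which the 3- and 6-week assessments are counted if they are timed from baseline, or randomisation moves to week 0, just before the first small-group session. No procedure is added and the sample size is unaffected.

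If neither is workable, state that allocation is concealed from patients and testers until baseline is recorded. That deals with the bias but not with the patient who leaves after randomisation and before any measurement; the article would then need to say how such a patient is handled in the intention-to-treat analysis.

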**Fig. 1 Fig1:**
[figure not shown]
Study design. The enrolled participants are to be randomly assigned to one of the three study conditions: endurance training; resistance training; active control, with assessments to be taken at three pre-specified time points

